##### High-throughput T-cell receptor sequencing

High-throughput sequencing (HTS) of the T-cell receptor (TCR) will be used to identify and quantify the distinct T-cell clone present within the biological samples. Therefore CDR3 region will be amplified and sequenced as described before [12, 13]. In brief, the method will use a multiplex PCR system to amplify all possible rearranges TCRβ CDR3 sequences from cDNA samples. Furthermore in a second step V and J gene primers will be used to amplify the rearranged VDJ segments which are subjected to HTS. Afterward the unique CD3 segment and the V,D, and J genes within each rearrangement will be identified and quantified using the ImmunoSEQ analyzer toolset and NCBI databases.

##### Suppression assay

CD4^+^CD25^+^CD127^dim/−^ regulatory T cells will be separated from responder T cells by magnetic-activated cell sorting using a CD4^+^CD25^+^CD127^dim/−^ Regulatory T Cell Isolation Kit II (Miltenyi Biotec). Responder T cells will be labeled with 5 μM carboxyfluorescein succinimidyl ester (CFSE; Invitrogen) according to the manufacturer’s instructions. Afterwards regulatory T cells and CFSE^+^ responder T cells will be cocultured at a ratio of 1:2 and 1:1, respectively. Cultures will be stimulated with anti-human CD3 (2 μg/ml; OKT3) and soluble mouse anti-human CD28 (1 μg/ml; eBioscience) for 4 days. After the stimulation period proliferation will be assessed by flow cytometry.

#### Additional endpoints

Furthermore, clinical related data as MRI scans and evaluation of disease activity and manifestation using EDSS and MSFC as well as data on number and time of relapses will be considered as additional endpoints.

##### Expanded disability status scale (EDSS)

Patient disability will be evaluated using the EDSS, which has long been considered the standard for assessing disability in patients with MS [14]. All involved physicians of the study team will be trained and certified to perform the EDSS in a consistent manner on www.neurostatus.net. The EDSS is an ordinal clinical rating scale which ranges from 0 (normal neurologic examination) to 10 (death due to MS) in half-point increments. Briefly, the assessing neurologist rates 7 functional systems (pyramidal, cerebellar, brainstem, sensory, bowel and bladder, visual, cerebral, and other) in the context of a standard neurological examination and then uses these ratings in conjunction with observations and information concerning the patient’s mobility, gait, and use of assistive devices to assign an EDSS score. EDSS steps 1.0 to 4.5 refer to people with MS who are fully ambulatory, while EDSS steps 5.0 to 9.5 are defined by the impairment to ambulation. The visual functional system score as determined as part of the assessments for EDSS will be considered as an additional endpoint.

##### Multiple sclerosis functional composite

The MSFC is a composite measure of impairment and acquisition of disability comprising quantitative tests of the function of the upper and lower limbs and cognitive abilities. Research to date has demonstrated that change in the MSFC over the first year of observation predicted a subsequent change in the EDSS, suggesting that the MSFC is more sensitive to change than the EDSS [14]. The Clinical Outcomes Assessment Task Force of the National MS Society developed the MSFC as a new scale for clinical outcomes measurements. The MSFC will be administered according to the MSFC manual of the National MS Society.

#### Sample size

At least 50 patients per group will be included in this study. The groups comprise three different groups: (i) de novo patients (until 04/2019), (ii) patients under alemtuzumab treatment and (iii) patients requiring more than two alemtuzumab infusions.

The sample size is justified by:

Cohen’s d (Δ/σ = difference of means/standard deviation) is a measure of effect size for mean differences of two groups with similar sample size. Cohen’s d is used to estimate the relevance of significant mean differences. The expected effect size can be estimated on the basis of data from previous studies:
Alemtuzumab leads to a decrease of absolute CD8^+^ T cell numbers in peripheral blood from 0,34 × 10^9^ ± 0,05 cells/L to 0,175 × 10^9^ ± 0,06 cells/L 6 months after treatment [15]. Here, Cohen‘s d equals 0,831.Alemtuzumab increases the concentration of BDNF (brain-derived neurotrophic factor) produced by peripheral blood mononuclear cells under MBP (myelin basic protein) stimulation from 200 ± 82 pg/mL to 290 ± 73 pg/ml 6 months after treatment [15]. Here, Cohen’s d equals 0,502.

Clinical studies define effect sizes of Δ/σ = 0,2–0,3 as small, Δ/σ = 0,3–0,8 as medium and Δ/σ > 0,8 as large. Based on previous data we are expecting medium to large effect sizes with a Cohen’s d of > 0,5. With a type I error of α = 0,05 and a power of 0,95 the required sample size equals 42.

The precision of this estimation is considered to be sufficient to track the condition of the immune system over time to describe the mechanisms of action of alemtuzumab treatment.

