### Limitations of the study

The approach of a multicentre study results in a higher rate of patient enrolment and improves the generalizability of the study. Nevertheless, multicentre studies have several disadvantages regarding the difference in the severity of the disease and the heterogeneity in clinical practice among centers, which is a major confounding factor for the interpretation of the results [21]. Therefore, a rigorous study protocol for uniform data collection was created. However, patient recruitment takes place in highly specialized centers for multiple sclerosis (centers of the Kompetenznetz Multiple Sklerose KKNMS) which might bias the patient pool, because these patients might have a more complicated and severe disease history, which could limit our results at least in part.

Furthermore, the outcome of the study might be influenced by the potential loss of follow ups. Patients who discontinue study participation or the treatment with alemtuzumab prematurely will not be replaced. To avoid an effect on the results we calculated that a sample size with at least 50 patients per each group (de novo patients; patients under alemtuzumab treatment; patients requiring more than two alemtuzumab infusions) is necessary to compensate potential loss of follow up.

Although we aim to elucidate the mechanism of action of the potential immune-reconstitutive effects of alemtuzumab within this study, the results might be limited since the data will only be generated from blood samples. Since the pathologic process of MS takes place in the CNS, it is still unknown how representative the lymphocyte populations/parameters in the peripheral blood samples may be, since the transmigration via the blood-brain barrier is a tightly regulated process and might be affected in disease and under therapy [22]. Further studies will be needed to characterize the immunological change and explore new biomarkers in the brain itself using animal models or potentially CSF analysis. However, the requirement for lumbar puncture constitutes a major barrier for more general use, especially when repeated lumbar punctures are needed.

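### The two planning values called Cohen's d are not d by the protocol's own definition, and d = 0.5, 95% power and n = 42 do not fit together

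*Protocol article*

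**What the plan says.** The protocol article, section Sample size, gives this definition: "Cohen’s d (Δ/σ = difference of means/standard deviation) is a measure of effect size for mean differences of two groups with similar sample size". It then takes two before-and-after effects from an earlier study.

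- CD8+ T cells fall from 0.34 ± 0.05 (× 10⁹ cells/L) to the level in "cells/L to 0,175 × 10^9^ ± 0,06 cells/L 6 months after treatment". The section adds: "Here, Cohen‘s d equals 0,831".
- BDNF production changes "from 200 ± 82 pg/mL to 290 ± 73 pg/ml 6 months after treatment". The section adds: "Here, Cohen’s d equals 0,502".

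Effects of 0.3–0.8 are called medium and those above 0.8 large. From the two examples the section concludes that "we are expecting medium to large effect sizes with a Cohen’s d of > 0,5". With α = 0.05 it then states "a power of 0,95 the required sample size equals 42". It names no test and no sidedness, and does not say whether 42 is a total or a number per group.

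The enrolment target is at least 50 in each of three groups. Limitations of the study ties that number to loss to follow-up: "we calculated that a sample size with at least 50 patients per each group". Statistical methods plans paired tests between two time points and repeated-measures models for longer series. It treats all inference as exploratory, with no significance level fixed.

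**The concern.** A mean difference of 0.165 with SDs of 0.05 and 0.06 is about three SDs, so it cannot give a d of 0.831. A difference of 90 with SDs of 82 and 73 exceeds one SD, so it cannot give 0.502. If the printed values are on another scale, the planning threshold of 0.5 was read off that scale and then used as a d.

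Three things are at stake. Later studies may take 0.831 and 0.502 into their own planning as Cohen's d. The medium-to-large description of the expected effects would be wrong. The stated 95% power would not belong to the stated effect size and number of patients.

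**Working it through.** **Inputs.** The means, ± values, α = 0.05, power 0.95, d = 0.5 and n = 42 all come from Sample size. The ± values are taken as SDs; the section does not label them.

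**1. Effect sizes by the protocol's definition.** d = |m₁ − m₂| / √((s₁² + s₂²)/2).

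- CD8+: pooled SD = √((0.05² + 0.06²)/2) = 0.0552; d = 0.165/0.0552 = 2.99.
- BDNF: pooled SD = √((82² + 73²)/2) = 77.63; d = 90/77.63 = 1.16.

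Using the baseline or the follow-up SD alone gives 3.30 or 2.75 for CD8+ and 1.10 or 1.23 for BDNF. No choice of SD gives 0.831 or 0.502.

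**2. Reproducing the printed values.** With r = d/√(d² + 4):

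- CD8+: 2.988/√(2.988² + 4) = 0.831.
- BDNF: 1.159/√(1.159² + 4) = 0.5015, which rounds to 0.502.

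Both printed figures are matched to three decimals.

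**3. Reproducing n = 42.** Numbers needed for 95% power at α = 0.05 (noncentral t):

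| Effect | Test | n |
|---|---|---|
| d = 0.5 | paired, two-sided (d scaled by SD of change) | 54 |
| d = 0.5 | paired, one-sided | 45 (normal approximation 44) |
| d = 0.5 | two-sample, two-sided | 105 per group |
| r = 0.5, i.e. d = 1.155 | two-sample, two-sided | 21 + 21 = 42 |

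In the last row, 20 + 20 gives power 0.945 and 21 + 21 gives 0.955, so 42 is the smallest equal-group total that reaches 0.95.

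**4. Power at d = 0.5, paired and two-sided.**

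- If 0.5 is the mean change divided by the SD of the change, power is 0.886 at n = 42 and 0.934 at n = 50.
- If 0.5 is on the raw SD scale that the definition uses, with equal SDs, the standardised change is 0.5/√(2(1 − ρ)), where ρ is the within-patient correlation. The protocol gives no ρ, so a range is shown for n = 42:

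| ρ | standardised change | power |
|---|---|---|
| 0 | 0.354 | 0.61 |
| 0.3 | 0.423 | 0.76 |
| 0.5 | 0.500 | 0.89 |
| 0.6 | 0.559 | 0.94 |
| 0.7 | 0.645 | 0.98 |

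**5. Power for the weaker cited effect.** At the BDNF value d = 1.16, paired with ρ = 0, the standardised change is 90/√(82² + 73²) = 0.82. Power at n = 42 is above 0.999.

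**6. What the fixed size delivers (two-sided).**

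- The standardised within-patient change detectable with 95% power is 0.57 at n = 42 and 0.52 at n = 50.
- The 95% CI half-width, t₀.₉₇₅,ₙ₋₁/√n, is 0.31 SD of change at n = 42 and 0.28 at n = 50.
- Comparing two groups of 42, 95% power is reached only at d of about 0.80.

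**The case against.** - **No test is named, so the origin of 42 is a reconstruction.** This stands. The match at r = 0.5 is exact and fits both mislabelled effects, but a reader should not take it as established. An unstated one-sided paired calculation comes close: 44 or 45 patients, with power 0.938 at n = 42. Even so, 42 falls short of 0.95, and the two cited effects move in opposite directions.
- **The shortfall depends on the scale of d.** This also stands. On the raw SD scale, 42 patients nearly reach 0.95 at a correlation of 0.6 and exceed it at 0.7. A reader might infer that 50 per group lies below a requirement of 54 and so leaves nothing for losses. That holds only on the SD-of-change, two-sided reading. The protocol also sets 50 as a minimum, and gives neither a loss rate nor a sum leading from 42 to 50.
- **The error understates the cited effects.** This is correct. A reader might infer that the study is underpowered, but its own figures do not support that for the two effects it cites.
- **Two-group figures are peripheral.** Statistical methods specifies no comparison among the three patient groups for the primary endpoints, so the 105 per group matters only if such comparisons are intended.
- **BDNF is not listed in Table 2.** It does relate to the neuroprotection aim, and CD8+ counts are a primary endpoint, so replacing the example is a matter of preference.
- **The study is exploratory.** No decision hangs on 95% power. That lowers the weight of the point but does not make the figures right.

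**Conclusion.** The point holds for the arithmetic of the justification, not for the adequacy of the study. The printed 0.831 and 0.502 are not Cohen's d as the protocol defines it. If the ± values are SDs, d is 2.99 and 1.16, both large by the protocol's own 0.8 cut-off. If they are another measure of spread, these two values change as well, so the source needs checking.

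The combination of d = 0.5, α = 0.05, 95% power and n = 42 is not reproduced by a paired or a two-sample t-test, one- or two-sided. For the planned paired comparisons the gap is modest on the SD-of-change scale, 0.886 against 0.95. On the raw SD scale it runs from a clear shortfall to none, depending on a correlation that is not given. The correction should be made, but in an exploratory study with no fixed significance level it is not critical.

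**What to change.** In Sample size:

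1. Confirm from the cited source that the ± values are SDs. Then either replace 0.831 and 0.502 with d = 2.99 and 1.16, or label them as effect-size correlations r.
2. Drop the medium-to-large description of these two effects.
3. Name the test, its sidedness, the SD that scales the effect, and whether 42 is a total or a number per group.
4. Replace the power statement with what the fixed size gives for a two-sided paired comparison: 95% power for a standardised within-patient change of 0.57 with 42 evaluable patients or 0.52 with 50, and about 89% power at 0.5 with 42.
5. Support the closing sentence on precision with the 95% CI half-widths of 0.31 and 0.28 SD of change.
6. If comparisons between patient groups are intended, state that 42 against 42 gives 95% power only for d of about 0.80.

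The cost is a rewritten paragraph and a slightly less favourable power statement. No extra patients and no change of design are needed.

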#### Statistical methods

Statistical analyses will be performed using standard statistical software like SAS or SPSS. The goal of this study is to detect the patterns in different populations of immune cells after treatment with alemtuzumab. Therefore, the analysis of the primary endpoints will focus on estimating the absolute and relative number of cells defined as primary endpoints summary statistics such as mean and standard deviation, median and quartiles, or frequency and percent, as appropriate. The development over time will be displayed using boxplots. To assess the difference of absolute or relative number of cells between two different time points statistical tests appropriate to the statistical distribution of the particular endpoint will be used (Wilcoxon signed-rank test, Student’s t-test for paired samples, Sign-Test). In order to compare more than two successive measurements, the preferred methods of statistical analysis are Repeated Measures ANOVA, Mixed Models and Generalized Estimation Equations, appropriately accounting for intra-individual correlations. Since this study is planned as an exploratory study, inferential statistics are intended to be exploratory (hypotheses generating), not confirmatory, and are interpreted accordingly. I.e., *p*-values are interpreted as a metric weight of evidence against the respective null hypothesis of no effect. Neither a global significance level nor local levels are determined. *P*-values are considered noticeable in case p < =0.05 and highly noticeable in case p < =0.01. These findings will be used to generate new hypotheses. Statistical analyses of the pre-specified secondary endpoints will be performed with appropriate descriptive and inductive statistical methods using summary statistics such as mean and standard deviation, median and quartiles, or frequency and percent. Appropriate to the characteristics of the endpoints, statistical tests like Fisher’s exact test, Chi-Square test, Mann-Whitney-U test, Wilcoxon signed-rank test or Student’s t-test will be performed.

### Eligibility criteria

The below-mentioned eligibility criteria imply that they are indicated to receive or are already treated with alemtuzumab irrespective of study participation. Patients who do not meet all the inclusion criteria listed in Table 3 or meet one of the exclusion criteria listed in Table 3 will be excluded from further study participation.

**Table 3 Tab3:** Eligibility criteria

Inclusion Criteria	
• Diagnosis of MS according to the McDonald criteria 2010 and cranial MRI scan demonstrating white matter lesions attributable to MS within 5 years before signing the informed consent form (ICF)	
• Age > 18 years	
• Written informed consent to study participation	
Exclusion Criteria	
• Medical, psychiatric, cognitive, or other conditions that, in the Investigator’s opinion, compromise the patient’s ability to understand the patient information, to give informed consent, or to complete the study	
• Any progressive form of MS	
• Any condition that serves as a contraindication for alemtuzumab treatment	
• Any disability acquired from trauma or another illness that could interfere with the evaluation of disability due to MS	
• Major systemic disease or other illness that would, in the opinion of the Investigator, compromise patient safety or interfere with the interpretation of study results, e.g., current peptic ulcer disease or other conditions that may predispose to hemorrhage	
• Significant autoimmune disease including but not limited to immune cytopenias, rheumatoid arthritis, systemic lupus erythematosus, other connective tissue disorders, vasculitis, inflammatory bowel disease, severe psoriasis	
• Inability to undergo MRI with gadolinium administration	

## Perspective

Alemtuzumab is a highly effective disease modifying therapy for RRMS, which selectively targets CD52, an antigen presented on the surface of T- and B cells, the main drivers of pathology in MS. However, the exact mechanism of action remains largely unknown [9]. Our study aims to elucidate further insights into these mechanisms by performing a deep characterization of changes in immune cell distribution and function under alemtuzumab treatment in RRMS. Thereby, our study will help to develop new strategies for the prediction of potential side effects and to identify patients with optimal response improving the individual risk-benefit ratio for alemtuzumab therapy.

Alemtuzumab leads to a depletion of lymphocytes following a slow repopulation with a distinct sequential pattern: B cells reach baseline levels after 3 months, overshooting them at 6 months. In contrast T cells repopulate much slower and CD4^+^ and CD8^+^ T cells typically need several years to reach pre-treatment levels [9]. Besides quantitative changes of the immune cell repertoire, also qualitative alterations of immune components are observed, e.g. within the first month there is predominance of immature B cells, whereas the differentiation into memory B cells is very slow [15]. Therefore, it was proposed that alemtuzumab leads to a reconstitution of the immune system promoting tolerogenic mechanisms [9].

Interestingly, Jones et al. reported that specific changes in the reconstituting T-cell pool are associated with secondary autoimmunity. Patients with secondary autoimmunity had no greater T cell lymphopenia in comparison to those without but displayed higher T-cell apoptosis and cell cycling by genetically determined higher levels of IL-21. This enhanced cycling leads to an increased stochastic opportunity for T cells to encounter self-antigens thereby promoting autoimmunity [16]. Furthermore, T-cell recovery after alemtuzumab treatment is characterized by the proliferation of self-antigen responsive T cells, which have escaped the depletion. This so-called homeostatic proliferation leads to the generation of chronically activated (CD28^−^CD57^+^), highly proliferative (Ki67^+^), oligoclonal, memory-like CD4^+^ and CD8^+^ T-cells (CCR7^−^CD45RA^−^ or CCR7^−^CD45RA^+^) producing proinflammatory cytokines [17].

Those studies showed first insights into the changes in different immune-cell population. However, the exact changes in the immune cell profile including T- and B-cell populations at the same timepoints over a long period still need to be characterized.

Long-term remission and EDSS improvement under alemtuzumab therapy also fuelled the theory of additional neuroprotective effects beyond the well-known anti-inflammatory activity of alemtuzumab [18]. Jones et al. could show that peripheral blood mononuclear cells (PBMCs), isolated from MS patients treated with alemtuzumab, have increased levels of neurotrophic molecules leading to improved neuronal survival, axonal growth and oligodendrocyte survival and maturation in vitro [18]. However, this was only shown for peripheral immune cells. Moreover, an in vivo animal model of multiple sclerosis, the MOG_35–55_ EAE, failed to reproduce the neuroprotective effect driven by immune cell derived brain-derived neurotrophic factor (BDNF) [19]. The definite mechanism of action of the potential neuroprotective effects or whether there are such are still unknown and will be further investigated in this study by combining clinical data (EDSS, MSFC), MRI (brain atrophy, structural integrity) and immunological analysis (ex vivo and in vitro data).

Recently, a safety review of the European Medicines Agency’s (EMA) was initiated since 39 patients had suffered from vascular events such as heart attacks or strokes under therapy with alemtuzumab. Currently, the review is still ongoing and the final report is anticipated by the end of the year [8]. However, secondary autoimmunity seems to remain the most relevant adverse effect of alemtuzumab with thyroid disorders, immune thrombocytopenia and immune-mediated nephropathies being most prevalent with the highest incidence 1–3 years after treatment initiation [20]. Biomarkers allowing to identify patients at risk for the development of secondary autoimmune diseases are currently not available. Therefore, new biomarkers and/or immune-signatures predicting secondary autoimmunity are needed to improve the safety profile of alemtuzumab. Our study will use in depth analysis of immune cell status over time to reveal potential new signatures of immune reconstitution, that might be able to predict secondary autoimmunity. However, since the study is limited to three years follow up, further validation of potential biomarkers will be needed for the long-term treatment with alemtuzumab.

### Limitations of the study

The approach of a multicentre study results in a higher rate of patient enrolment and improves the generalizability of the study. Nevertheless, multicentre studies have several disadvantages regarding the difference in the severity of the disease and the heterogeneity in clinical practice among centers, which is a major confounding factor for the interpretation of the results [21]. Therefore, a rigorous study protocol for uniform data collection was created. However, patient recruitment takes place in highly specialized centers for multiple sclerosis (centers of the Kompetenznetz Multiple Sklerose KKNMS) which might bias the patient pool, because these patients might have a more complicated and severe disease history, which could limit our results at least in part.

Furthermore, the outcome of the study might be influenced by the potential loss of follow ups. Patients who discontinue study participation or the treatment with alemtuzumab prematurely will not be replaced. To avoid an effect on the results we calculated that a sample size with at least 50 patients per each group (de novo patients; patients under alemtuzumab treatment; patients requiring more than two alemtuzumab infusions) is necessary to compensate potential loss of follow up.

Although we aim to elucidate the mechanism of action of the potential immune-reconstitutive effects of alemtuzumab within this study, the results might be limited since the data will only be generated from blood samples. Since the pathologic process of MS takes place in the CNS, it is still unknown how representative the lymphocyte populations/parameters in the peripheral blood samples may be, since the transmigration via the blood-brain barrier is a tightly regulated process and might be affected in disease and under therapy [22]. Further studies will be needed to characterize the immunological change and explore new biomarkers in the brain itself using animal models or potentially CSF analysis. However, the requirement for lumbar puncture constitutes a major barrier for more general use, especially when repeated lumbar punctures are needed.

